#### Interim analyses {21b}

Although there are no anticipated problems that may be detrimental to the participants, serious life-threatening adverse events leading to prolonged hospital stay or death will be reported to the Institutional Review Board (IRB) and our study will be terminated immediately. There will be no interim analyses in this trial.

#### Methods for additional analyses (e.g., subgroup analyses) {20b}

Prior to statistical analysis, a sub-investigator will review the data record forms to check for their legitimacy and identify the missing data. The subgroup analysis will be conducted to evaluate outcomes in patients based on their baseline clinical and demographic characteristics such as gender, age, type of hematoma in CT scan, antithrombosis, and comorbidity.

#### Methods in analysis to handle protocol non-adherence and any statistical methods to handle missing data {20c}

All researchers will be trained referring to the same training protocol. Protocol modifications will not be expected. Missing clinical data, if any, will be obtained from the electronic hospital files. Postoperative follow-up evaluation at specified time points is mandatory and missing data are not to be anticipated. Analyses of all outcomes will be performed according to the intention-to-treat principle, and once enrolled, all participants will be analyzed, regardless of the findings.

#### Plans to give access to the full protocol, participant-level data, and statistical code {31c}

Data collected will be kept in the online EDC system. Only the research members and the IRB of all study sites will have access to the files. After the completion of the study, the results will be made public through publication in a scientific journal along with conferences related to neurosurgery, and the clinicaltrials.gov website. The data generated or analyzed during this study will be available from the corresponding author on reasonable request.

### Oversight and monitoring

#### Composition of the coordinating center and trial steering committee {5d}

The coordinating center (CC) will comprise of a PI, two neurosurgeons, and one methodologist. The role of CC is training of the research members from all study sites regarding every aspect of the study protocol including recruitment, preoperative evaluation, intervention, and follow-up evaluation, along with the coordination and supervision of all standardized data management and quality control.

The Trial Steering Committee (TSC) will include three independent neurosurgery experts and two independent statisticians. It will be responsible for recruitment and progress of the trial, overall supervision, and quality control during the study, and ensure standardized training for research members regarding the study protocol.

#### Composition of the data monitoring committee, its role and reporting structure {21a}

An independent DSMB consists of two statisticians and two clinical experts. All members are blinded and independent of the study and investigators. The DSMB will monitor the study data, participant safety, and SAEs throughout the trial and be responsible for all the statistical work. The DSMB will regularly report blinded statistical data to TSC, and subsequent meetings will be held at every 25%, 50%, 75%, and 100% of participant inclusions with interim analyses.

### Adverse event reporting and harms {22}

The IRB of all 19 study sites will supervise the trial progress annually. Any adverse events will be recorded, and a thorough assessment of the potential association between the study interventions and the adverse event will be carried out. Serious life-threatening AEs leading to prolonged hospital stay or death will be reported to the IRB and the trial will be terminated immediately.

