### Criteria for discontinuing or modifying allocated interventions {11b}

The allocated interventions cannot be modified during study participation, and crossover to the other study arm is not allowed. Cessation of the treatment is mandatory if a suspected serious adverse event (SAE) occurs, or participants request to withdraw from the study. Participants can withdraw their consent at any time and terminate their participation in the study prematurely. Withdrawal from the study and detailed reasons will be recorded if known. Moreover, the principal investigator (PI) is entitled to terminate the study prematurely if patient recruitment remains inadequate, or unacceptable risks arise after assessment by the Data Safety Monitoring Board (DSMB).

A detailed recording of all the adverse events (AEs) during the study will be closely monitored, and reported to the ethics committee as soon as possible, with the intention of a resolution or stabilization, or even termination of the study if necessary.

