#### Secondary outcome

Secondary outcomes include functional outcome (modified Rankin Scale, mRS score [10] and Markwalder Grading Scale, MGS grade [11]) at baseline, and at 1, 3, and 6 months; quality of life (five-dimensional EuroQol, EQ-5D-5L [12]) at baseline, and at 1, 3, and 6 months; mortality at 6 months; and rate of complications and adverse events between groups within 6 months.

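### Two sections require immediate termination of the trial on serious life-threatening adverse events, with no count, relatedness or DSMB condition, which conflicts with the discretionary DSMB route and the planned mortality outcome

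*Protocol article*

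**What the plan says.** Two sections of the protocol article state a mandatory rule. Adverse event reporting and harms {22} reads: "Serious life-threatening AEs leading to prolonged hospital stay or death will be reported to the IRB and the trial will be terminated immediately". Interim analyses {21b} says of the same kind of event that "our study will be terminated immediately". The sentence before the rule in {22} promises that "a thorough assessment of the potential association between the study interventions and the adverse event will be carried out", but termination is not made to depend on the result.

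Criteria for discontinuing or modifying allocated interventions {11b} is worded differently. Adverse events are reported to the ethics committee with a view to resolution or stabilization, "or even termination of the study if necessary". Separately, the principal investigator is entitled to end the study if recruitment is inadequate or if "unacceptable risks arise after assessment by the Data Safety Monitoring Board (DSMB").

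Three other sections bear on this:

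- Composition of the data monitoring committee {21a} has the DSMB monitoring serious adverse events throughout, with meetings at 25%, 50%, 75% and 100% of inclusions. It states that "All members are blinded and independent of the study and investigators" and gives the board responsibility for all statistical work.
- Secondary outcome, under Outcomes {12}, lists "mortality at 6 months" and the rates of complications and adverse events between groups.
- Who will be blinded {17a} names data analysts among the blinded roles.

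**The concern.** A mandatory, immediate stop and a discretionary stop after review give different answers to the same event. If a participant dies of a life-threatening adverse event, {21b} and {22} say that the trial is over, while {11b} says that someone decides. Sites, ethics committees and the DSMB could each cite a section in support of opposite actions.

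The mandatory version also conflicts with the trial's own aims. Patients may be up to 90 years old and all undergo surgery, and mortality is to be compared between arms at 6 months. A rule that ends the trial at a fatal adverse event would defeat that comparison and could end the trial before the recurrence question is answered.

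If the rule is not applied literally, the weight falls on the DSMB assessment in {11b}. The article does not say what the board is blinded to, so a reader cannot tell whether it will see serious events and deaths split by arm.

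**Working it through.** **Step 1: the provisions side by side**

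| Section | Consequence for the trial | Condition |
|---|---|---|
| {22} | Immediate termination | Serious life-threatening events leading to prolonged stay or death; no count, relatedness, arm or DSMB condition |
| {21b} | Immediate termination | Same kind of event; same conditions absent |
| {11b}, adverse events | Termination only where needed | Judgement after reporting to the ethics committee |
| {11b}, principal investigator | Entitled to terminate | Unacceptable risk after DSMB assessment, or inadequate recruitment |
| {21a} | DSMB monitoring through 100% of inclusions | None stated |
| Secondary outcome | Mortality and between-group event rates over 6 months | Presupposes that the trial continues after deaths |

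The first two rows leave no room for the next three. This conflict needs no numerical assumption.

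**Step 2: the planned size**

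Inputs from Sample size {14}: recurrence 10% versus 2%, power 80%, alpha 5% (taken as two-sided), dropout 10%. With pooled variance under the null and mean proportion 0.06:

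n = [1.960 × √(2 × 0.06 × 0.94) + 0.842 × √(0.10 × 0.90 + 0.02 × 0.98)]² / 0.08² = 137.2, rounded up to 138 per group.

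That is 276 in total, and 276 × 1.10 = 303.6, giving 304. The stated size reproduces, and 304 is the denominator used below.

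**Step 3: how often a literal rule would fire**

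The documents give no rate for the trigger event, so the per-patient 6-month risk p is an assumption shown over a range. Events are treated as independent. The chance of at least one among 304 patients is 1 − (1 − p)^304.

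Some of these events would occur after the last patient is enrolled and could not prevent enrolment of 304. The last column therefore counts only events before the last enrolment. It assumes even accrual over 30 months (December 2020 to May 2023, from Study setting {9}) and events spread evenly over each patient's 6 months. The chance is then 1 − Π[1 − p × min(1, rᵢ/6)], where rᵢ is the number of months from patient i's enrolment to the last enrolment.

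| Assumed p | At least one event among 304 | Median patient at first event | At least one before last enrolment |
|---|---|---|---|
| 0.25% | 53% | 277 | 50% |
| 0.5% | 78% | 138 | 75% |
| 1% | 95% | 69 | 94% |
| 2% | 99.8% | 34 | 99.6% |

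The median is ln(0.5)/ln(1 − p). Over the full follow-up of 304 patients, a 90% chance needs p of about 0.75%, and a 95% chance needs about 0.98%.

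**Step 4: the nearest figure in the documents**

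In the investigators' own series, 1117 − 1092 = 25 patients (25/1117 = 2.2%) were not at mRS 0–3 at 6 months. This group includes disabled survivors. It is at most a ceiling on deaths in that series and not a rate for the trigger. The printed 97.0% beside 1092/1117 also does not match that fraction, which is 97.8%. The figure is therefore not used as an input.

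**The case against.** The strongest reply is that the literal reading is too harsh. The text speaks of events in the plural and sets no count, so stopping at the first event is an interpretation. The trigger is narrower than any life-threatening event, because it must lead to prolonged stay or death. A relatedness assessment stands in the sentence before the rule, and the authors may have meant it to come first. These points stand as cautions. But the text makes nothing conditional on that assessment, gives no number and says that termination is immediate, and the rule appears in two sections. A charitable reading has to supply conditions that the article does not contain.

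Three stronger conclusions are tempting, and the documents do not support them.

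- A reader might infer that the trial is almost certain never to reach 304 patients. That depends on a risk of about 0.75% to 1% or more, and no rate is given. At 0.25% it is roughly an even chance.
- A reader might infer that a blinded DSMB cannot compare harm between arms, so that no working safety process exists. {21a} does not say what members are blinded to. The blinded data it mentions are those reported to the steering committee, and review by coded arm is not excluded. Such detail may also sit in a charter that is not shown.
- A reader might infer that {11b} allows termination only on a DSMB recommendation. It entitles the principal investigator to stop after DSMB assessment, also allows stopping for poor recruitment, and separately mentions termination following adverse events. It describes no binding recommendation.

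On the statistical work, {17a} does not say whether its data analysts are the DSMB statisticians or other people, so overlap of the roles is unclear and not established.

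**Conclusion.** The point holds as an internal contradiction. {21b} and {22} order immediate termination without conditions, {11b} makes termination a matter of judgement, and the DSMB's remit and the mortality outcome both presuppose a trial that continues past such events. This is a stated rule that is wrong as written, and it cannot be excused as detail left to another document.

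The practical size is conditional. If the rule is applied at the first event and the per-patient risk is between 0.25% and 2%, it would fire with a probability of about 53% to 99.8% over the trial, or about 50% to 99.6% before the last enrolment. Early stopping is therefore probable over most of that range, but its probability cannot be fixed from the documents. What the DSMB is blinded to, and who carries out the analysis, are ambiguities to clear up and not demonstrated failures.

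**What to change.** Reconcile {21b} and {22} with {11b} in one trial-level termination provision, stated once and cross-referenced. It should say who decides, on what assessment, and how the promised relatedness assessment enters. It must also be compatible with DSMB monitoring throughout {21a} and with the 6-month mortality outcome. Which rule to adopt is for the sponsor and its committees; no particular rule is proposed here.

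In the same edit:

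- State in {21a} what DSMB members are blinded to, so that the risk assessment foreseen in {11b} can compare serious adverse events and deaths between arms, at least by coded arm.
- Reconcile the DSMB's responsibility for all statistical work with the blinded data analysts named in {17a}.

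The cost is an amendment to wording and, if a DSMB charter exists, matching text there. Sample size, data collection and committee membership do not change.

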### Frequency and plans for auditing trial conduct {23}

The IRB of all study sites will be making regular inspections of trial conduct. The inspections will be independent from the investigators and the sponsor. Data management researcher will stay in regular contact with the investigators about trial progress, data consistency, and follow-up visit violations.

### Plans for communicating important protocol amendments to relevant parties (e.g., trial participants, ethical committees) {25}

Although changes or amendments are not to be expected, any trial deviations from the present protocol will be fully documented using a breach report form. Protocol amendments will be notified to the sponsor within 3 days and then to the relevant parties and centers by sending the updated protocol to the investigators. Any changes must be cleared in written form and signed by all persons in charge, stating the detailed reasons for changes. If necessary, changes must be approved by the IRB and/or individual participants. A copy of the revised protocol will be added to the Investigator Site File. The protocol will be updated on the ClinicalTrials.gov registry website.

#### Dissemination plans {31a}

After the completion of the study, the results will be written as a final trial report through publication in a scientific journal along with international meetings related to neurosurgery, and the clinicaltrials.gov website.

## Discussion

The recurrence of CSDH is a major challenge, and the optimal treatment strategy to reduce the incidence of recurrence is limited although many associated risk factors have been reported [13–18]. There is solid evidence that postoperative drainage is effective in reducing symptomatic recurrence of CSDH, which is generally performed in CSDH burr-hole surgery. However, standard drainage strategy remains a matter of debate, and fixed-time drainage strategy is widely accepted, which is defined as 24 or 48 h of drainage period [8, 19–21]. Even so, according to literature, the recurrence rate is still relatively high (5–33%) with this strategy. Our observational evidence suggests that a postoperative exhaustive drainage strategy may reduce the incidence of recurrence without major complications. Thus, a randomized controlled trial is needed to evaluate the effectiveness of exhaustive drainage compared to fixed-time drainage.

In this study, we describe the rationale, design, interventions, and methodological framework of a multicenter, open-labeled, randomized controlled trial to test whether an exhaustive drainage strategy can reduce the rate of recurrence in CSDH compared with a fixed-time drainage strategy. Furthermore, we will investigate functional outcome (mRS and MGS) and quality of life (EQ-5D-5L) in the period prior to and after surgery. Moreover, the economic impact of different drainage strategies will be analyzed.

Our study has several strengths. First, our primary endpoint tests the efficacy of exhaustive drainage versus fixed-time drainage after burr-hole craniostomy in an effort to reduce the recurrence of CSDH. Second, outcome parameters that measure the functional outcome, quality of life, and healthcare-related costs are included. Third, this study will conduct in 19 neurosurgical centers in China, and all patients at 18–90 years are included. Therefore, we believe the results will be widely applicable.

In conclusion, we have developed a protocol for a multicenter, open-labeled, randomized clinical trial to evaluate the efficacy of an exhaustive drainage strategy. This study will provide an answer to whether an exhaustive drainage strategy can reduce CSDH recurrence and improve clinical outcomes, which may change clinical practice and guideline recommendations.

### Trial status

This research protocol version 1.0 (2020/07/31) is approved, and recruitment of patients for this ECHO trial has begun in December of 2020 and is expected to complete in December of 2023.

## Data Availability

After the completion and following the publication of the ECHO trial, requests for data sharing will be considered by the ECHO trial Management Group.

## Abbreviations

AE: Adverse event
CSDH: Chronic subdural hematoma
CC: Coordinating center
CONSORT: Consolidated standards of reporting trials
CT: Computerized tomography
DSMB: Data safety monitoring board
EDC: Electronic data capture
ICH-GCP: International conference on harmonization-good clinical practice
IRB: Institutional review board
MGS: Markwalder grading scale
mRS: Modified rankin scale
PI: Principal investigator
SAE: Serious adverse event
TSC: Trial steering committee
